#### Relevant concomitant care permitted or prohibited during the trial {11d}

Practitioners in both the intervention and control groups will be advised that best practice in treating depression is not to start treatment at the consultation at which symptoms of a new episode are presented by the patient, unless they think it is absolutely indicated in their clinical judgment. This is because a significant proportion of patients will improve without treatment within 2–3 weeks, having had their problems acknowledged and having received general advice about the nature and course of depression. We are interested in this study with the use of the PHQ-9 when deciding on initial treatment, as well as follow-up monitoring, so we prefer treatment not be started before the baseline assessment in both groups and before the first PHQ-9 questionnaire has been administered by the researcher in the intervention group. In the feasibility study, this baseline assessment was carried out on average 10 days (range 1–38 days) from receiving the patient’s reply slip, so completion of this baseline assessment within 2 weeks of the patient’s first presentation should be possible in most cases.

However, patients recruited either opportunistically or via the weekly searches possibly will have been started on treatment at the consultation, when they first presented with a new episode, if treatment cannot be postponed in the judgement of the treating practitioner. We will record whether treatment has already started at the baseline assessment.

#### Provisions for post-trial care {30}

No harm or compensation is anticipated for trial participation.

### Outcomes {12}

The primary outcome is the symptom score on the Beck Depression Inventory second edition BDI-II [36] for the current level of depression at the 12-week follow-up. Secondary outcomes are the BDI-II score at 26 weeks, anxiety on the GAD-7 measure of generalised anxiety disorder [37], and scores at both 12 and 26 weeks on the Work & Social Adjustment Scale [38] for social functioning, the EuroQol 5-item 5-level (EQ-5D) questionnaire for quality of life [39] and the number and amounts of drug treatments and referrals for depression over the 26 weeks of total follow-up, as determined using a modified version of the Client Service Receipt Inventory [40] to calculate NHS costs. In addition, a modified version of the Medical Informant Satisfaction Scale MISS [41] will be administered at 26 weeks to measure patient satisfaction over the follow-up period.

The Beck Depression Inventory, second edition BDI-II is a 21-item self-report instrument that uses DSM-IV criteria [36]. It has been established as a valid and reliable instrument for depression screening in the general population [36, 42] and is widely used in depression trials. It takes approximately 5 minutes to complete. Each item is scored from 0 to 3, and a total score of 0–13 is considered minimal range, 14–19 is mild, 20–28 is moderate, and 29–63 is severe.

The Work and Social Adjustment Scale (WASA) assesses problems in functioning with work, home management, social leisure activities, private leisure activities and family and relationships, all on 0 to 8 scales [38]. It has been shown to be a sensitive, reliable and valid measure of impaired functioning and is used routinely in IAPT psychological therapy settings as well as in research studies in a variety of settings.

The EuroQol-5D (EQ-5D)-5 L measure of health-related quality of life [39] is the measure favoured by NICE in determining cost-effectiveness when developing its clinical guidelines. The EQ-5D includes five dimensions: mobility, self-care, usual activities, pain/discomfort, and anxiety/depression, each scored on five levels. Health states are converted into a single summary index by applying weights to each level in each dimension derived from the valuation of EQ-5D health states in adult general population samples [43]. The EQ-5D measure of patient utility will be used to determine changes in quality adjusted life years (QALYs) for the health economics evaluation.

Costs will be calculated from responses to the Client Service Receipt Inventory CSRI [40], modified specifically for the study. A review of participating patients’ digital medical records will also be carried out by practice staff after the 26-week follow-up, to augment questionnaire measurement of health and social service resource use using the modified CSRI.

The 29-item ‘Medical Interview Satisfaction Scale’ (MISS-29) was developed in the USA to assess patient satisfaction with individual doctor-patient consultations and has been shown to be valid and reliable in UK primary care [41]. We will adapt it to rate patient satisfaction at the 26-week follow-up, asking patients to look back over their consultations with GPs/NPs over the entire 26-week period.

#### Participant timeline {13}

### Sample size {14}

We need a sample large enough to detect a difference between arms at follow-up of the minimal clinically important score (MCID) on the primary outcome: the Beck Depression Inventory 2nd edition (BDI-II).

Button et al. [44] used data collected from three randomised controlled trials (*n* = 1039) for the management of depression and compared improvement on a ‘global rating of change’ question with changes in BDI-II scores. They used general linear modelling to explore baseline dependency, assessing whether MCID is best measured in absolute terms (i.e., difference) or as percentage reduction in scores from baseline (i.e., ratio). The modelling indicated that MCID is best measured on a ratio scale as a percentage reduction of score, and an MCID of a 17.5% reduction from baseline was identified from receiver operator characteristics analyses as the optimal threshold above which individuals reported feeling ‘better’ [44].

In the PROMDEP feasibility trial, we found the mean BDI-II score at baseline was 24.0, and the standard deviation (SD) was 10.0 [18]. At the 12-week follow-up, based on the results of the feasibility study, we anticipate a mean of 14.0 in the intervention group and 17.0 in the control group. This gives a mean difference of 3.0 on the BDI-II, which is an effect size of 0.3 SDs and agrees with the findings of Knaup et al’s systematic review for the expected effects of combined practitioner and patient feedback of PROMs [16]. The difference of 3.0 points is 17.6% of the control group’s score of 17.0 at 12 weeks, and therefore, this score is just above the MCID for the BDI-II [44]. The anticipated potential benefit would therefore be small but clinically significant.

We aim to recruit a mean of six patients per practice. We assume an intra-cluster correlation coefficient (ICC) of 0.03 (from the feasibility study). At the level of 5% significance, to have 90% power to detect a difference between 14.0 and 17.0 on the BDI-II we need 235 patients analysed per group. Given a cluster size of six, the cluster design effect will be 1.15, meaning we need 270 per group. We assume a 20% loss to follow-up at 12 weeks, so the total sample size needed will be 270 × 2/0.8, which is a total of 676 patients recruited from 113 practices across the three recruitment centres (around Southampton, UCL and Liverpool).

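### The 3.0-point target is called clinically important by applying a within-person, change-from-baseline MCID to the control group's 12-week mean; on the baseline the section itself gives, 3.0 points is 12.5%, not 17.6%

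*Protocol article*

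**What the plan says.** All of this is in the protocol article, Sample size {14}.

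- The purpose of the calculation is to "detect a difference between arms at follow-up of the minimal clinically important score (MCID) on the primary outcome".
- The MCID comes from pooled data of three trials, where "an MCID of a 17.5% reduction from baseline was identified from receiver operator characteristics analyses". It is described as the "optimal threshold above which individuals reported feeling" better, so it is a threshold for change within one person.
- From the feasibility trial, "the mean BDI-II score at baseline was 24.0, and the standard deviation (SD) was 10.0".
- For 12 weeks, "we anticipate a mean of 14.0 in the intervention group and 17.0 in the control group". The target is therefore 3.0 points, or 0.3 SD, and a systematic review of PROM feedback is cited as agreeing with an effect of that size.
- The target is then compared with the MCID as "17.6% of the control group’s score of 17.0 at 12 weeks, and therefore, this score is just above the MCID".
- The section concludes: "The anticipated potential benefit would therefore be small but clinically significant".

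**The concern.** The threshold is defined on one base and applied on another. A fall of 17.5% from baseline is a statement about baseline scores, and the section supplies the baseline mean two sentences before it makes the comparison. The 3.0 points are nevertheless divided by the expected control mean at 12 weeks, a smaller number, and the result lands 0.1 percentage points above the threshold.

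There is also a change of level. The threshold marks when an individual feels better than before. The target is a difference between two group means at the same time point. Nothing in the section explains how the first becomes the second.

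What is at stake is interpretation. This comparison is the section's only link between the target and clinical importance, and the section's opening sentence makes that link the reason for the sample size. If it stands, 3.0 points is likely to be treated as the MCID when the result is discussed.

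**Working it through.** **Inputs** (all from Sample size {14}): MCID 17.5% reduction from baseline; baseline mean 24.0; SD 10.0; expected 12-week means 14.0 (intervention) and 17.0 (control); 5% significance; 90% power; ICC 0.03; six patients per practice; 20% loss. Sidedness is not stated; two-sided is assumed, and it reproduces the plan's figure. Equal baseline means in the two arms are also assumed.

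**1. The plan's own figures**

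- Percentage: (17.0 − 14.0)/17.0 = 3.0/17.0 = 17.6%. Reproduced.
- Sample size per group for 3.0 points, SD 10.0: 234 by the normal approximation; 234.5 by the t-test, rounded up to 235. Reproduced.
- Design effect: 1 + (6 − 1) × 0.03 = 1.15; 235 × 1.15 = 270.25.
- Total: 270.25 × 2/0.8 = 675.6, so 676; 676/6 = 112.7, so 113 practices. Reproduced.

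**2. The target on the base used to define the MCID**

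- 3.0/24.0 = 12.5%.
- 17.5% of baseline: 0.175 × 24.0 = 4.2 points, or 0.42 SD.
- 3.0/4.2 = 71%.
- Baseline mean at which 3.0 points would equal 17.5%: 3.0/0.175 = 17.1, well below 24.0.
- For comparison, 17.5% of the control 12-week mean: 0.175 × 17.0 = 2.975, just under 3.0.

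**3. The threshold applied to change within each arm, as it was defined**

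| Arm | Expected mean fall | % of baseline |
|---|---|---|
| Control | 24.0 − 17.0 = 7.0 | 29.2% |
| Intervention | 24.0 − 14.0 = 10.0 | 41.7% |
| Difference | 3.0 | 12.5 percentage points |

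Both mean falls exceed 17.5%. The threshold therefore does not separate the arms at the level of means and says nothing about whether the 3.0-point gap matters.

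**4. Does the choice of base affect the design?**

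- Effective number per group: 270/1.15 = 234.8.
- Power for 3.0 points: about 90%.
- Power for 4.2 points: about 99.5%.
- A 4.2-point target, other inputs unchanged, would need 120 per group by the normal approximation; 120 × 1.15 = 138; 138 × 2/0.8 = 345 in total, against 676 planned.

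So the planned sample is ample on either reading.

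**The case against.** The best defence is a ratio reading. The section says the MCID is better expressed as a percentage than as an absolute difference. With equal baselines, the ratio of the fractions of the score remaining is (14/24)/(17/24) = 14/17 = 0.824, a 17.6% relative reduction against control. Baseline cancels and the control mean becomes the natural denominator. On this view 12.5% is only the additive version of the same contrast.

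The arithmetic of that defence is sound, and it is a reason to report 17.6% with its proper label. It does not rescue the conclusion. The section does not offer the argument, it defines the percentage as a reduction from baseline, and the ratio reading would still carry an individual change threshold over to a contrast between groups.

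The cited review does not fill the gap either. It is used to support the size of effect to be expected, not its clinical importance.

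Three stronger readings are tempting, and the document does not support them:

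- *The sample size is wrong or the trial is underpowered.* Every step reproduces, and power is higher, not lower, for 4.2 points.
- *Any statistically significant difference would be reported as clinically significant.* The statistical methods sections set no such rule, and the sentence in question concerns only the anticipated 3.0 points.
- *4.2 points is the correct between-arm MCID, so the confidence interval should be judged against it.* That repeats the same transfer from within-person to between-arm. The 4.2 figure shows that the section's comparison fails on its own base, and no more than that.

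**Conclusion.** The claim that 3.0 points clears the MCID, and the inference to clinical significance, are wrong as written. On the base that the section defines, the target is 12.5% against a threshold of 17.5%, or 3.0 points against 4.2. On the level that the section defines, the threshold does not bear on a between-arm difference at all.

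The error is confined to the clinical-importance justification. The individual division 3.0/17.0 is correct, and the sample size, the number of practices and the power stand. It does not follow that a 3.0-point difference is unimportant, only that the cited threshold does not show it to be important.

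The figures rest on the feasibility trial's baseline mean of 24.0 applying to both arms. The direction of the conclusion would change only if the mean baseline were about 17.1 or lower.

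**What to change.** Keep the sample size and the 3.0-point (0.3 SD) target. In Sample size {14}:

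1. Delete the statement that the target exceeds the MCID and the inference to clinical significance that follows from it. Reword the opening aim so that it no longer promises a sample built on the MCID.
2. State that 3.0 points is 12.5% of the expected baseline mean and 17.6% relative to the expected control mean at 12 weeks.
3. State that the cited 17.5% is an individual change-from-baseline threshold and does not directly set a between-arm MCID.
4. Justify the target as a plausible small effect worth having because the intervention is cheap. The article already makes that case in its Background and Discussion.
5. Do not use 3.0 points as the MCID when interpreting the result.

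A comparison of the proportions with at least a 17.5% fall from their own baseline would use the threshold at the level where it was defined. It is at most an optional supplementary analysis for the SAP and is not needed to correct this point.

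The cost is a change of wording, with no extra patients and no change of design. The downside is that the stated justification becomes less favourable.

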### Recruitment {15}

#### Method 1

Where possible, patients who are seen with a new episode of depressive symptoms or disorder will be recruited opportunistically during consultations by participating GPs and NPs in both arms of the study. Patients identified through this method will be given the information sheet by hand, along with a reply slip and a Freepost envelope, and will be asked to contact the study team if they wish to take part.

#### Method 2

Method 1 may be subject to selection bias by the GP/NP; therefore, to guard against this, we will identify all patients presenting with a new episode of depressive symptoms or disorder through weekly searches of practice medical records databases to find patients who were not selected for approach by the GP/NP. In the feasibility trial, both methods were used and 79% of patients were recruited in consultations opportunistically, and 21% through the weekly database searches, but the method used varied by practice, and some practices recruited the majority of patients through the weekly searches.

Our experience gained while recruiting people with depression for previous studies has shown that approximately 120 Read codes are used by GP/NPs, including diagnostic codes (e.g., major depressive disorder) and symptom codes (e.g., low mood). Practices will use the full list for searching their databases weekly. Patients identified through this method will be mailed an information sheet about the study by the practice and asked to contact the study team if they wish to take part, or to decline, using a reply slip and a Freepost envelope. If they do not respond, the research team will have no knowledge of them, maintaining patient confidentiality.

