## Trial design {8}

The study is a parallel group, cluster-randomised, controlled, superiority trial, with patients clustered by participating practices, and 1:1 allocation of practices to intervention and control groups. We chose a cluster-randomised design after a feasibility study that showed that randomising patients individually within practices risks contamination between study arms.

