### Who will take informed consent? {26a}

Patients identified as potentially eligible in clinic consultations will be given an information sheet by hand, together with a reply slip and a Freepost envelope, and they will be asked to contact the study team if they wish to take part after they have had time to consider. To avoid selection bias by the GP/NP, patients presenting with a new episode of depressive symptoms or disorder will also be identified through weekly searches of practice medical records databases for the identification of patients who were not selected by the GP/NP. Patients identified through this method will be mailed an information sheet about the study by the practice and asked to contact the study team if they wish to take part, or to decline, again using a reply slip and a Freepost envelope, after they have had time to consider. If they do not respond, the research team will have no knowledge of them, maintaining patient confidentiality, and this will not prejudice their future treatment. If patients do respond positively to either approach, a member of the research team will then contact them, screen them by telephone for any exclusion criteria, and arrange to see them face to face for a baseline visit if they are eligible. At the baseline visit, the researcher will go over the patient information sheet again and seek formal written consent.

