### Assignment of interventions: blinding

#### Who will be blinded {17a}

Blinding of both patients and practitioners in the intervention arm is impossible given the nature of the intervention. Self-report outcome measures are therefore being used to prevent observer rating bias by research team members aware of the patient’s assigned trial arm. The statisticians and health economists analysing the data are being kept blind to the allocation.

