### Statistical methods

#### Statistical methods for primary and secondary outcomes {20a}

A full and detailed statistical analysis plan will be developed prior to the final analysis of the study. The main features of the statistical analysis plan are as follows:

The primary outcome, that is, the differences at 12 weeks between intervention and controls in depression as measured by the BDI-II, will be analysed using a linear mixed model, adjusting for socio-demographics, baseline depression, anxiety, and clustering, including practice as a random effect. The model will use all the observed data and makes the assumption that missing BDI-II scores are missing completely at random.

Analysis of secondary outcomes, BDI-II at 26 weeks, social functioning, patient satisfaction and quality of life score, will also be conducted using linear regression for continuous outcomes and logistic regression for dichotomous outcomes, again adjusting for socio-demographics, baseline depression, anxiety, and clustering, including practice as a random effect.

A health economic evaluation will be undertaken from a National Health Service and Personal Social Service perspective, with a sensitivity analysis from a societal perspective. The outcome will be expressed as incremental cost per point improvement in the BDI-II clinical outcome, and incremental cost per quality adjusted life year (QALY) gained (cost utility analysis). All items will be costed using appropriate data (e.g., PSSRU NHS and social care reference costs [45]), with informal care costed at minimum wage level. The primary analysis will be at 26 weeks. Personal costs will include patient and carer time off work, personal expenses and travel.

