A generalised linear mix model will be used to estimate the differences in costs and QALYs (using the EQ-5D to calculate patient utilities), adjusting for baseline characteristics including depression history, quality of life and sociodemographic factors. Where appropriate, we will estimate incremental cost-effectiveness ratios (ICERs). We will estimate mean values and 95% percentiles using non-parametric bootstrapping, and use these to produce cost-effectiveness acceptability curves (CEACs). Major assumptions in the costing and QALYs analysis will be tested through sensitivity analyses. Modelling of the likely benefit, if any, of using PROMs in practice will include making assumptions about the extra time which would have to be taken for GPs/NPs to administer the initial PROM (rather than the researcher) in the non-trial situation, together with any payments that might have to be made to practices, e.g., through the QOF, to incentivise the use of PROMs.

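### Practitioner selection after allocation can only be partly prevented, yet the clinical models omit depression history, which the economic model already adjusts for

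*Protocol article*

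**What the plan says.** The unit of allocation is the practice, with "1:1 allocation of practices to intervention and control groups" (Trial design {8}). Under Recruitment {15}, Method 1, patients "will be recruited opportunistically during consultations by participating GPs and NPs in both arms of the study". On blinding, the article says: "Blinding of both patients and practitioners in the intervention arm is impossible given the nature of the intervention" (Who will be blinded {17a}).

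The article acknowledges the consequence and answers it with Method 2: "Method 1 may be subject to selection bias by the GP/NP; therefore, to guard against this, we will identify all patients". The consent section {26a} gives the same purpose: "To avoid selection bias by the GP/NP, patients presenting with a new episode of depressive symptoms or disorder will also be identified". In the feasibility trial, "79% of patients were recruited in consultations opportunistically, and 21% through the weekly database searches", and the same sentence adds that some practices recruited most of their patients through the searches.

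Statistical methods {20a} describes the primary BDI-II model as "adjusting for socio-demographics, baseline depression, anxiety, and clustering, including practice as a random effect" and repeats that adjustment for the secondary clinical outcomes. Later in the same section, the model for costs and QALYs is described as "adjusting for baseline characteristics including depression history, quality of life and sociodemographic factors".

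**The concern.** In a cluster trial, randomising practices balances practices. It does not balance patients who are identified afterwards by people who know the arm. Trained intervention practitioners might approach a somewhat different kind of patient from control practitioners. Minimisation uses practice size, location and centre, so it cannot correct that.

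The weekly search helps by inviting patients whom the practitioner did not approach. Two gaps remain. It finds only patients to whom the practitioner has given a relevant Read code, and it brings in only those who return a mailed slip. Non-responders stay unknown to the research team.

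Some residual patient-level imbalance is therefore possible, and adjustment for prognostic baseline variables is the analysis tool that remains. Depression history is such a variable by the trial's own account, since the economic model adjusts for it. Leaving it out of the primary model forgoes protection at almost no saving. It also means clinical effects and costs in the same patients are adjusted differently. The economic outcomes include a cost per BDI-II point, so the two halves of that ratio could rest on different covariate sets.

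**Working it through.** **1. The plan's own figure (Sample size {14}).** Inputs: difference 3.0, SD 10.0, 5% significance (taken as two-sided), 90% power, ICC 0.03, six patients per practice, 20% loss.

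- Per group before clustering: 2 × (1.960 + 1.282)² × (10/3)² = 233.5, so 234. The t-based value is 234.5, so 235, as stated.
- Design effect: 1 + (6 − 1) × 0.03 = 1.15, and 235 × 1.15 = 270.25. The article uses 270.
- Total: 270 × 2 / 0.8 = 675, or 676 with each arm rounded up to 338. Practices: 676 / 6 = 112.7, so 113.

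The sample size reproduces and is not in question. It implies a standard error for the primary contrast of 10 × √(2 × 1.15 / 270) = 0.92 points, before any gain from covariates.

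**2. The covariate lists in {20a}.**

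| Baseline item | BDI-II and other clinical outcomes | Costs and QALYs |
|---|---|---|
| Socio-demographics | listed | listed |
| Baseline depression | listed | not named |
| Anxiety | listed | not named |
| Depression history | **not listed** | **listed** |
| Quality of life | not listed | listed |

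The economic list is introduced as including certain items, so it may be incomplete. The clinical list carries no such word.

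**3. What an imbalance in history would do.** Bias = (difference between arms in prevalence of prior depression) × (effect of history on 12-week BDI-II, given the listed covariates). Neither input is in the documents, so both are assumed. The two-sided type I error with bias b is Φ(−1.96 − b/0.92) + 1 − Φ(1.96 − b/0.92).

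| Imbalance | Effect of history | Bias (points) | Share of 3.0 | Type I error |
|---|---|---|---|---|
| 5 pp | 2 | 0.10 | 3% | 5.1% |
| 10 pp | 3 | 0.30 | 10% | 6.2% |
| 20 pp | 3 | 0.60 | 20% | 10.0% |
| 20 pp | 5 | 1.00 | 33% | 19.2% |

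If the imbalance arose only among patients recruited by practitioners, at the feasibility share of 79%, each bias shrinks by that factor. For example, 0.30 × 0.79 = 0.24. The direction is unknown.

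**4. What adjustment gains in precision.** A yes/no covariate with effect c explains at most c²/4 of the outcome variance. With c = 3 that is 2.25 out of 10² = 100, so the standard error falls at best from 0.92 to about 0.92 × √0.9775 = 0.91. The proportional gain is somewhat larger against the residual variance left after the baseline score. It is a real gain but a small one.

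**5. Whether estimating the effect by recruitment route would help.** Search-recruited patients at the feasibility share: 0.21 × 676 = 142. After 20% loss: 142 × 0.8 = 114, about 57 per arm. Standard error, ignoring clustering: 10 × √(2/57) = 1.87. The 95% interval is ±1.96 × 1.87 = ±3.7 points, wider on each side than the 3.0-point target. Route is also settled after allocation, partly by unblinded practitioners, so estimates within route can themselves be biased.

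**The case against.** The strongest reply is that the two recruitment methods together aim to invite every coded new presentation in both arms. A practitioner's preference then no longer decides who is invited, and a researcher, not the practitioner, screens for exclusions and takes consent. This largely stands: the search is a real safeguard. A reader might infer from the 79/21 split that it is nearly powerless. The split does not show that. It is a share of patients recruited, not of patients approached, from 47 patients in nine practices, in a study that tested individual as well as cluster randomisation. What the reply leaves open is selection through coding and through differing response to a mailed and a hand-given invitation.

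A second reply is that symptom scores and costs may properly have different covariates, so the two lists do not contradict each other. That is also fair. The point is not an inconsistency for its own sake. A prognostic variable judged worth adjusting for in one model is available at no cost to the other. No passage suggests that practitioners would select on history, and the listed baseline scores may already absorb much of any such selection.

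A third reply is that the article gives only main features and leaves detail to an analysis plan not shown. This rules out complaint about baseline tables or sensitivity analyses by route. It would also be wrong to infer that route goes unrecorded. The covariates of the primary model, however, are stated as one of those main features and can be judged as written.

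Two points of reading remain. That control practitioners know their arm is inferred from allocation by practice and from the abstract's statement on blinding. Baseline depression is taken here as the symptom score.

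**Conclusion.** The point holds as a modest improvement that costs almost nothing. Patient recruitment follows allocation, part of it runs through unblinded practitioners, and the search reduces the resulting selection without fully removing it. The clinical models in {20a} omit a baseline variable that the economic model uses.

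The documents do not establish that the primary estimate is biased, and a reader should not infer it. The figures of 0.3 and 0.6 points rest entirely on an assumed imbalance of 10 or 20 percentage points and an assumed 3-point effect of history given the other covariates. The 1.0-point case needs both assumptions at the top of their ranges. At 0.3 points the bias is about a third of the standard error. The documents also do not support reading the search as a failed safeguard, and no change to its description is needed.

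**What to change.** Pre-specify depression history as a covariate in the primary BDI-II model and in the secondary clinical models, defined as it will be for the cost and QALY model. If *baseline depression* in {20a} is already meant to include history, say so there instead.

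The cost is one covariate and a line in the analysis plan. Sample size, visits, data collection and clinical care do not change, assuming history is collected as the economic model requires. The gain is a small improvement in precision, less influence from measured imbalance in history, and closer alignment of the clinical and economic adjustments. It does not cure selection on unmeasured characteristics. An effect estimate by recruitment route is not recommended, for the reasons in step 5 of the working, and the article plans no subgroup analyses.
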